### 2.9 Statistical analysis

#### 2.9.1 Primary analyses

In Part 1, the effect of the OLP on the AUPC will be tested using a two-sample *t*-test. In order to account for additive period effects, the estimator of the treatment effect will be built as follows: The mean of the difference in the AUPC between the first and the second visit will be calculated for all patients who receive the placebo in the second visit. Then, the mean of the difference in the AUPC between the first and the second visit will be calculated for all patients who receive the placebo in the first visit. Then, the difference of the first and the second mean will be calculated and divided by two.

In Part 2, the AUPCs of the three groups will be compared as follows: First, the mean of the AUPC in the “Booster” groups (fixed-time and on-demand) will be compared to the mean of the AUPC in the control group using a two-sample *t*-test. If the test yields a significant difference, the mean of the AUPC in the fixed-time “Booster” group will be compared to the mean of the AUPC in the on-demand “Booster” group using a two-sample *t*-test.

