In accord with the pain model, two microdialysis catheters with internal stainless-steel wires will be inserted in parallel (5 mm apart) into the intradermal, volar surface of the forearm (not used for venous access) for a length of approximately 10 mm (Figure 3). The catheters will be filled with 0.9% saline set to a continuous flow of 0.4 μl/min, ensured by a syringe pump, to facilitate conduction and to protect the tissue from eventual pH changes by the direct current. To ensure comparability of electrode nociceptor distance regarding subcutaneous tissue thickness after intracutaneous electrode placement only participants with a BMI between 18 and 25 were included. The stainless-steel wires will be attached to a constant current stimulator in combination with a pulse generator. This installation applies monophasic, rectangular electrical pulses 0.5 ms in duration with alternating polarity at a frequency of 2 Hz. The pulse generator pauses the stimulation for 30 s after conducting 500 pulses (approximately 4 min). The current will be increased to target a pain rating of 6 out of 10 on the NRS. Three further adjustments in current will be made every 5 min for the next 15 min to compensate for habituation. The final current will be kept constant until the end of the particular experiment. The total duration of electrical stimulation will be 200 min for Part 1; for Part 2, the duration of stimulation will depend on the results of Part 1. For sure, for ethical, technical and logistic reasons, there will be a limit to the observation time. This time limit will not substantially exceed the duration of stimulation that we know is safe for the skin, i.e., 200 min. At the end of the experiment, the current will be stopped, microdialysis catheters and venous access removed, thereby ending the study visit.

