#### 2.4.3 Randomization

As every participant in Part 1 will receive all of the possible treatments, we are only able to randomize the order of the treatments, and thereby control for excitement and habituation effects.

For Part 2, group allocation will be randomized (control group, fixed-time “Booster” group, on-demand “Booster” group).

Randomization will be performed by study staff not involved in study assessments using a random number generator.^1^

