### 2.8 Sample size

For Part 1, we estimated how many participants are needed to achieve an 80% power to detect a difference of 45 in the AUPC between the interventional visit and the control visit. Based on data from our previous study (55), we assumed a standard deviation of 67 for the differences in the AUPC. The assumed difference and standard deviation of the difference correspond to a Cohen’s d of 0.7. Calculations were done assuming a two-sided alpha of 5% and using a two-sample *t*-test for comparison. The number of participants needed for Part 1 is 36.

The sample size for Part 2 was determined with respect to the comparison of the combined “Booster” (i.e., fixed-time and on-demand) groups *vs*. the control group. Including 105 participants allows to estimate a difference in the AUPC of 45 between the “Booster” groups and the control group and a difference of the AUPC of 51 between the fixed-time and on demand group with a power of 80%.We assume a standard deviation of 76 for the AUPC in all groups, which corresponds to a Cohen’s d of 0.6. Calculations were done assuming a two-sided alpha of 5% and using a two-sample *t*-test for comparison.

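### The Part 2 primary t-tests leave out the pain rating already collected before the first injection: the tests are valid, but they give up some precision.

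*Protocol article*

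**What the plan says.** **Endpoint.** Section 2.6 defines the primary endpoint as the area under the NRS curve after the OLP injection. It is a raw area, not a change from the level before the injection. In Part 2 the time span is to be derived from Part 1.

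**Primary tests.** For Part 2, section 2.9.1 begins "In Part 2, the AUPCs of the three groups will be compared as follows". The pooled booster groups are compared with control by a two-sample t-test. If that is significant, fixed-time is compared with on-demand by another. For Part 1 it says "In Part 1, the effect of the OLP on the AUPC will be tested using a two-sample" t-test, applied to between-visit differences by sequence. Neither test has a covariate.

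**Sample size.** Section 2.8 uses the same unadjusted test: "Calculations were done assuming a two-sided alpha of 5% and using a two-sample" t-test. For Part 2, "Including 105 participants allows to estimate a difference in the AUPC of 45 between the" booster groups and control, and "a difference of the AUPC of 51 between the fixed-time and on demand group with a power of 80"%. The spread is given as "We assume a standard deviation of 76 for the AUPC in all groups".

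**Starting pain.** Tables 1 and 2 schedule the NRS at 0, 5, 10, 15 and 20 min, and section 2.5.1 places the first injection at 20 min. Section 2.4.2.2 raises the current towards an NRS of 6 and adds: "Three further adjustments in current will be made every 5 min for the next 15 min to compensate for habituation". The current is then fixed for the rest of that experiment.

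**Other models.** Sections 2.9.2 and 2.9.3 list the predictors for the regressions: questionnaire scores, time between visits, age, sex and education. Starting NRS is not among them.

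**The concern.** The outcome variable is measured before treatment, and this measurement is then left out of the analysis. In Part 2 that matters more than in Part 1, because no participant serves as his or her own control and the contrast carries the full between-person spread of the AUPC.

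Titration aims at a common pain level but need not reach it exactly. Since the current is then frozen, a participant who settles above or below 6 may stay there, and the AUPC would add up that offset over the whole observation time. A covariate that explains part of this spread reduces the residual variance and corrects the estimate for whatever imbalance chance produces between arms.

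There is little slack to give away. The planned power is 80%, and the second comparison is reached only if the first is significant.

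**Working it through.** **Inputs.** From section 2.8: SD 76, differences 45 and 51, two-sided alpha 5%, N = 105. Section 2.4.3 says "For Part 2, group allocation will be randomized" but the article gives no ratio, so 35 per arm is assumed (70 against 35 in the pooled test). The correlation r is not in the document, and a range is shown.

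**1. The plan's own figures.** Power is taken from the noncentral t distribution.

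- Pooled booster against control: SE = 76 × √(1/70 + 1/35) = 15.73. Noncentrality = 45 / 15.73 = 2.86 on 103 df. Power is 80.9%, and the smallest N in equal thirds that reaches 80% is 105. The stated figure is reproduced.
- Fixed-time against on-demand: SE = 76 × √(2/35) = 18.17. Noncentrality = 51 / 18.17 = 2.81 on 68 df. Power is 79.0% (80.2% by the normal approximation), which agrees with the stated 80% apart from rounding and method.

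**2. With the pre-injection NRS as covariate.** Residual SD = 76 × √(1 − r²), with one df fewer for each test.

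| r (assumed) | Residual SD | Power, difference 45 | Power, difference 51 |
|---|---|---|---|
| unadjusted | 76.0 | 80.9% | 79.0% |
| 0 | 76.0 | 80.9% | 79.0% |
| 0.2 | 74.5 | 82.4% | 80.6% |
| 0.3 | 72.5 | 84.4% | 82.6% |
| 0.4 | 69.7 | 87.1% | 85.5% |

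The r = 0 row shows the price of a useless covariate: no change at this rounding. If all three arms are fitted in one model, the residual df is 105 − 4 = 101 for both contrasts. That leaves the first column of power unchanged and raises the second by less than half a percentage point.

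**3. Both tests in sequence.** If both assumed differences hold, and arms are equal so that the contrasts are orthogonal, the chance of succeeding on both is roughly the product: 0.809 × 0.790 = 64% unadjusted, 0.824 × 0.806 = 66% at r = 0.2, and 0.871 × 0.855 = 74% at r = 0.4.

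**4. Chance imbalance.** If the starting NRS has an SD of 0.5, 1.0 or 1.5 points after titration (assumed), its difference between 70 and 35 participants has a standard error of SD × √(1/70 + 1/35), or 0.10, 0.21 or 0.31 points. How much of this reaches the AUPC depends on how long it persists and on the AUPC unit. The article gives neither, so the range of r in step 2 is the better summary.

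**5. Part 1.** With 18 participants per sequence, SD 67 for the within-person differences and the half-difference estimator of section 2.9.1: SE = ½ × 67 × √(2/18) = 11.17. Noncentrality = 45 / 11.17 = 4.03 on 34 df, and power is about 97%.

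**The case against.** **The plan is consistent with itself.** Part 2 is sized on an unadjusted t-test with SD 76 and analysed by that test, and the primary contrast reaches its power. That stands. A reader might infer that leaving out starting pain biases the comparison or invalidates the tests. It does neither: allocation is random, and the standard error of the t-test already allows for chance imbalance.

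**Titration already controls starting pain.** Everyone is brought towards NRS 6 with three further adjustments, which narrows the spread of the covariate and probably keeps r modest. This also stands, and it is why the table stops at 0.4. A reader might be drawn to r = 0.5, where power would be 90.5% and 89.2% and the gain would equal 105 / (1 − 0.25) = 140 participants. Nothing in the protocol supports a correlation that high.

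**The covariate may not be clean.** This is the most useful objection.

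- The last current adjustment falls at about 15 min on a natural reading of section 2.4.2.2, so the 15-min rating may belong to a different current. Averaging it with the 20-min rating is unsafe.
- Table 2 puts the 20-min rating, the questionnaires and the injection in the same column without an order.
- The article does not say when Part 2 participants learn their allocation. They are unblinded, and section 2.5.2 has controls reminded of their role after randomisation. A rating given with that knowledge could reflect expectation or disappointment, and adjusting for it could introduce bias. Since all arms receive the first injection, this is the more serious of the two ordering questions.

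These points determine which rating may be used. They do not remove the case for adjustment.

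**Part 1 does not need it.** Agreed. Within-person differencing removes stable differences between people, and only visit-to-visit differences in titration remain.

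**It may be in the analysis plan.** A supportive adjusted analysis could be there. The primary test, however, is fixed in the article, and it is unadjusted.

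**Conclusion.** The point holds for Part 2 as lost efficiency. Section 2.9.1 fixes unadjusted t-tests on the raw AUPC although a pre-injection rating of the same variable is collected and used nowhere. For r between 0.2 and 0.4, adjustment would add about 1.5 to 6 percentage points of power on each comparison. At r = 0 it would add nothing and cost almost nothing.

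These figures rest on 35 per arm, the stated SD of 76 and an assumed r. The existence of the omission is certain from the text; its size is not. The stated sample size of 105 is not in error. The change is worth making because it is nearly free and the second comparison has no margin, not because the planned analysis would mislead.

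**What to change.** **Part 2.** Make the primary analysis a linear model of AUPC on arm (three levels) and pre-injection NRS. Keep the same two contrasts in the same order: pooled boosters against control, then fixed-time against on-demand only if the first is significant. Retain the t-tests as sensitivity analyses.

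**Covariate.** Use a single NRS rating on the final current, after the last adjustment, for example the 20-min rating. State that it is recorded before the injection and before the participant learns the allocation. If the 20-min rating does not meet both conditions as the visits are run, name one that does, or leave the primary analysis unadjusted.

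**Part 1 (optional).** Regress the between-visit AUPC difference on sequence and on the between-visit difference in pre-injection NRS. Half the sequence coefficient, with the sign set as in section 2.9.1, is the planned estimator, adjusted.

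**Cost.** One degree of freedom and a few lines of analysis text, with no new measurements, visits or participants. Recruitment was under way when the article was written, so the model and the covariate should be fixed before any Part 2 outcome data are examined.

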This randomized study aims to fill the gaps in characterizing the efficacy of OLPs in acute pain. We will measure subjective pain ratings and areas of hyperalgesia and allodynia in a well-established experimental pain model (61) and investigate analgesia elicited by OLP injections accompanied by a short evidence-based treatment rationale, as in a previous study (55). To achieve this goal, Part 1 of our study will examine the duration of OLP analgesia and reevaluate the onset and size of the effect. Given the “inert” nature of OLPs, we assume that results of El Brihi et al. (31) concerning OLP dose effects on participant well-being will be generalizable to all outcomes and will, therefore, not evaluate different OLP dosages. Nevertheless and as stated above, multiple doses of placebos and more frequent intake increase effects (59, 60). Furthermore, participants given a choice over their (deceptive) placebo treatment experience enhanced placebo effects (62). For example, participants in control of the time point of administration of their placebo treatment experienced more placebo analgesia than participants without this control [(63); please note: this study investigated deceptive placebos and used conditioning effects]. This leads us to Part 2 of our study in which we will compare outcomes between participants receiving one OLP injection, participants receiving one repetition of the injection at a fixed time point, and participants receiving one repetition of the injection on demand (i.e., the last group will choose if and when they would like to receive the placebo “Booster”). This form of multiple-dose study aims to fill knowledge gaps concerning OLPs.

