##### 2.1.2.1 Primary objective

We hypothesize that there will be a difference in overall subjective pain ratings when comparing subjects receiving a repeated (i.e., two OLP injections) vs. a single OLP injection.

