**FIGURE 1 F1:**
[figure not shown]
Study design, part 1.

#### 2.2.2 Part 2

The second part of this study has been designed as a proof-of-concept, randomized, controlled, three-arm trial in a single center setup at the University Hospital of Basel. We will compare the effects of an OLP “Booster” inter-individually by analyzing three groups: A fixed-time “Booster” group (who will receive a first OLP at the beginning of the study visit and a second one at a time point derived from Part 1), an on-demand “Booster” group (who will receive a first OLP at the beginning of the study visit and a second one when participants ask for it), and a control group (who will receive only one OLP at the beginning of the study visit). Due to organizational reasons, blinding of the assessor will not be possible in Part 2.

The study design for Part 2 of this study is also shown in Figure 2.

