### 2.6 Outcome measures

A timeline of the assessments is shown in Tables 1, 2 for Part 1 and Part 2, respectively.

#### 2.6.1 Part 1

The primary endpoint of Part 1 is the area under the pain curve (AUPC) measured over 3 h according to an 11-point NRS following OLP administration. AUPC will be compared between the interventional visit (after receiving an OLP injection) *vs*. the control (non-interventional) visit.

Secondary endpoints of Part 1 are the differences between subjective pain ratings at each measurement point (NRS score every 5 min after OLP administration), the areas under the curve (AUCs) of area of hyperalgesia and area of allodynia, comparing the interventional *vs*. control (non- interventional) visit.

Hyperalgesia and allodynia will be measured immediately after pain ratings every 10 min as soon as an NRS of 6 is reached for the first time. Pinprick hyperalgesia will be assessed using a 256 mN von Frey filament and allodynia will be determined using a dry cotton swab. Measurements will be conducted from a more distant to a more central site along four orthogonal lines (distal, proximal, lateral, and medial) that will be drawn onto the skin with tick marks indicating each centimeter. Distal and proximal measurements will begin 12 cm from the site of electrical stimulation, and lateral and medial measurements 6 cm from the site. In both cases, the used measuring tool will be moved toward the site of stimulation in 1 cm increments until the subject reports either increased pain sensations from the von Frey filament (hyperalgesia) or an unpleasant “rougher” sensation from the cotton swab (allodynia). To create an area from these linear measurements, we are assuming that the areas are elliptical. The area is calculated using the formula $\frac{1}{4}\,\pi \times D\times d$ (D = proximal/distal diameter; d = medial/lateral diameter). For calculation reasons, we define 1 cm as the smallest value for the diameters.

#### 2.6.2 Part 2

The primary endpoint for Part 2 of our study is the AUPC (after OLP administration, as mentioned above) using the NRS during a time span derived from Part 1. We will compare the AUPCs of participants receiving a single OLP injection, participants additionally administered one repeated OLP injection at the time point derived in Part 1, and participants administered a second OLP injection on-demand.

Secondary endpoints of Part 2 are the same as those for Part 1 of the study.

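### Part 2's pooled booster test is valid but does not isolate two injections versus one, and neither booster arm is tested against control

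*Protocol article*

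**What the plan says.** Section 2.1.2.1 of the protocol article gives the Part 2 primary objective as a difference in overall pain ratings when "comparing subjects receiving a repeated (i.e., two OLP injections) vs. a single OLP injection".

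The on-demand arm does not guarantee a second injection. The Introduction says that "the last group will choose if and when they would like to receive the placebo" booster, and section 2.2.2 says that this arm gets "a second one when participants ask for it".

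Section 2.9.1 fixes two tests on the area under the pain curve (AUPC):

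1. The mean of the combined booster "groups (fixed-time and on-demand) will be compared to the mean of the AUPC in the control group", by two-sample t-test.
2. "If the test yields a significant difference, the mean of the AUPC in the fixed-time" arm is compared with that in the on-demand arm.

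Section 2.9.2 carries the same scheme over to hyperalgesia and allodynia. Section 2.6.2 names all three groups when it describes the comparison ("We will compare the AUPCs of participants receiving a single OLP injection", followed by the two booster groups), but no planned test sets one booster arm against control. Section 2.8 sizes Part 2 on the pooled contrast.

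**The concern.** The objective is about the number of injections, whereas the test is about allocation to one of two booster strategies. The two coincide only if everyone in the on-demand arm asks.

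The strategies also differ in more than timing. The Introduction argues that control over when a placebo is given strengthens its effect, so the on-demand arm combines possible repetition with choice. Pooling it with the fixed-time arm mixes the two mechanisms.

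At stake is the claim that the trial can make. It could end with a significant primary result and still have no test showing that a scheduled second injection does anything, or that the on-demand offer does. The Discussion presents the question of repeated versus single dosing as the novelty of the study.

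**Working it through.** **Inputs.** From section 2.8: 105 participants, SD 76 in all groups, two-sided alpha 5%, a difference of 45 for boosters versus control and 51 for fixed-time versus on-demand, power 80%. The allocation ratio is not stated; 35 per arm is assumed.

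**1. The plan's own figure.** The standard error is SD × √(1/n₁ + 1/n₂).
- Pooled, 70 versus 35: 76 × √(1/70 + 1/35) = 15.73; 45/15.73 = 2.86; power 80.9% (noncentral t, 103 df). The total needed by this method is 105.
- Fixed-time versus on-demand, 35 versus 35: 76 × √(2/35) = 18.17; 51/18.17 = 2.81; power 79.0% (t) or 80.2% (normal approximation).

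The stated size reproduces, so the arithmetic is sound.

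**2. What the pooled test can and cannot show.** Write F, O and C for the arm means, signed so that larger means more benefit. The pooled contrast is P = (F + O)/2 − C. The planned 45 arises from gains of 45 and 45, but equally from 0 in fixed-time and 90 on-demand: (0 + 90)/2 = 45. In the second case the pooled test is still significant in about 74% of simulated trials, although the scheduled second injection does nothing.

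**3. What the second test adds.** It tests D = F − O. A significant D does not show whether the worse booster arm beats one injection, and a non-significant D does not show that both do.

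**4. Error rate if arm-versus-control tests are added behind the pooled gate.** There are three pairwise null hypotheses.
- If any two are true, all three means are equal. The pooled null is then also true, and the gate lets at most 5% of trials through.
- If exactly one is true, only that one can be falsely rejected, and it is tested at 5%.

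So each can be tested at the full 5%. Simulation agrees: about 5% under the global null and with one true pairwise null.

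**5. Power of fixed-time versus control at a difference of 45.** Ungated: 45/18.17 = 2.48, power 68.5%. Behind the gate, by simulation:

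| On-demand arm | Mean gain in that arm | Gated power, fixed-time vs control |
|---|---|---|
| Gains as much as fixed-time | 45 | 66% |
| 30% never ask and gain nothing | 0.7 × 45 = 31.5 | about 60% |
| 50% never ask and gain nothing | 0.5 × 45 = 22.5 | about 52% |

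The shares of non-askers, and zero gain in them, are assumptions; the document gives no expected uptake. In the last two rows, gated power for on-demand versus control is below 40% and below 25%. Ungated 80% power for one arm versus control at 45 would need 46 per arm, 138 in total.

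**The case against.** The pooled contrast is prespecified, randomised and the basis of the sample size, and it keeps its type I error. Section 2.2.2 presents Part 2 modestly: "The second part of this study has been designed as a proof-of-concept, randomized, controlled, three-arm trial". Sections 2.1.2.1 and 2.1.2.2 promise repeated versus single and on-demand versus fixed-time, and section 2.9.1 supplies one test for each. No objective promises an arm-by-arm comparison with control. Arm-level point estimates also follow from the two planned contrasts, since F − C = P + D/2 and O − C = P − D/2. Estimates by arm, reporting of uptake and handling of non-askers may sit in an analysis plan that is not shown.

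Much of this stands, and it rules out three stronger readings.

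- *The test cannot answer the question at all.* Not supported. With full uptake the pooled contrast matches the stated objective in number of injections. With partial uptake it remains a valid comparison of offering a booster with a single injection.
- *Non-askers are simply control participants.* Not supported. They match control in injection count only. They hold a choice that control participants lack, and section 2.5.2 expects control participants to be disappointed.
- *The primary test is underpowered.* A reader could calculate that 30% or 50% non-askers cut the pooled effect to 38.25 or 33.75 and power to 67% or 57%. But that reads 45 as a full-uptake effect, whereas section 2.8 states it as the difference between the booster groups and control. The calculation also uses an uptake that the document does not give.

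What the objection does not remove is that section 2.9.1 fixes the tests, and neither of them supports a claim about one booster regimen against a single injection.

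**Conclusion.** The point holds in a limited form. Part 2's primary test validly compares booster strategies with one injection, but it does not isolate two injections versus one as section 2.1.2.1 words the question. A significant result cannot be attributed to repetition at a fixed time or to the on-demand offer, and the second step cannot settle this without control.

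That much follows from the text alone. The 74% figure illustrates how far a significant result can mislead about the fixed-time arm; it assumes 35 per arm, SD 76 and effects of 0 and 90. The power figures for the added tests depend on the same arm size and SD and, where non-askers enter, on assumed uptake. The point concerns what may be concluded, not the validity of the primary test or its sample size. The change should be made.

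**What to change.** - Keep the pooled test at two-sided 5% as the gate. If it is significant, test fixed-time versus control and on-demand versus control, each at two-sided 5%, beside the planned fixed-time versus on-demand test.
- Analyse by randomised arm, whether or not an on-demand participant asked.
- Describe the pooled result as the effect of offering a booster, and reword section 2.1.2.1 to agree with the optional second injection. Base any claim about two injections versus one on fixed-time versus control.
- Report the share of the on-demand arm that asked.

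This takes two extra tests and some wording, with no extra participants and no loss of alpha. The downside should be stated with it: the arm-level tests are not powered at 80%, and gating the fixed-time contrast behind the pooled test costs more power the less the on-demand arm gains. A non-significant arm-level result must not be read as evidence of no effect, so report each arm's difference from control with its confidence interval.

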##### 2.1.2.2 Further objectives

In addition, we hypothesize that, in comparison to receiving a repeated OLP injection at a fixed time point, overall subjective pain ratings will be different when subjects receive the second application of OLP on-demand. Moreover, we hypothesize that there will be a difference in areas of hyperalgesia and allodynia when comparing subjects receiving a repeated OLP injection (i.e., two OLP injections) with subjects receiving only a single injection of OLP and when comparing subjects receiving the second application at a fixed time point with subjects receiving the second application on demand.

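### Part 2 primary t-test merges the two booster arms, so any real difference between them inflates the error variance: a minor power loss that a three-arm contrast removes at no cost

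*Protocol article*

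**What the plan says.** Section 2.9.1 (Primary analyses) sets two steps for Part 2. First, the booster "groups (fixed-time and on-demand) will be compared to the mean of the AUPC in the control group using a two-sample" t-test. The second step depends on the first: "If the test yields a significant difference, the mean of the AUPC in the fixed-time" arm is compared with the on-demand arm, again by a two-sample t-test. Section 2.9.2 applies the same analysis to the hyperalgesia and allodynia AUCs.

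Section 2.8 (Sample size) bases the Part 2 sample size on the combined booster groups against control. "Including 105 participants allows to estimate a difference in the AUPC of 45 between the" combined boosters and control, and "a difference of the AUPC of 51 between the fixed-time and on demand group with a power of 80" percent. It adds: "We assume a standard deviation of 76 for the AUPC in all groups". The test is two-sided at 5%.

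Section 2.1.2.2 (Further objectives) hypothesises that, compared with a fixed-time second injection, "overall subjective pain ratings will be different when subjects receive the second application of OLP on-demand". It gives neither direction nor size.

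The article states no Part 2 allocation ratio. Section 2.4.3 says only that a random number generator is used.

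**The concern.** A two-sample t-test on merged arms treats the 70 booster participants as one homogeneous sample. If the two boosters have different true means, the distance between those means is counted as noise, on top of the within-arm SD of 76. The standard error is then larger than the sampling error of the estimate, so the test rejects less often than it could.

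This matters a little more than usual for two reasons. The plan itself hypothesises that the boosters differ. The merged test is also the gate to the fixed-time versus on-demand comparison, so the gate becomes harder to pass when the second hypothesis is true.

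There is a side effect on what is estimated. The merged mean weights each booster by its number of participants. With equal arms that is one half each. With unequal arms the target depends on the final counts.

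**Working it through.** **Inputs.** From Section 2.8: N = 105, SD 76 in every group, two-sided alpha 5%, differences of 45 (combined boosters vs control) and 51 (fixed-time vs on-demand). Assumed: 35 per arm and normally distributed AUPC. Pairing a mean effect of 45 with a gap of 51 (booster effects 70.5 and 19.5) is a construction for this check. The plan does not state that the two hold together.

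**Step 1: the plan's own figures.**
- 70 vs 35: standard error 76 × √(1/70 + 1/35) = 15.73; noncentrality 45/15.73 = 2.86; exact power 80.9%.
- 35 vs 35: standard error 76 × √(2/35) = 18.17; noncentrality 51/18.17 = 2.81; exact power 79.0% (80.2% by the normal formula).

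The stated 80% therefore reproduces, and equal arms fit it.

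**Step 2: variance used by the merged test.** With gap D, the SD within the merged booster group is √(76² + (D/2)²). At D = 51 this is √(5776 + 650.25) = 80.2. The pooled variance of the t-test (103 df) is on average about

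76² + 70 × (D/2)²/103.

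At D = 51: 5776 + 441.9 = 6217.9, an SD of 78.9 and 7.7% more variance than 5776.

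**Step 3: power at D = 51.** The test uses a standard error of 78.85 × 0.2070 = 16.32, so it rejects beyond 1.983 × 16.32 = 32.38. The estimate has mean 45 and true standard error 15.73. Power ≈ P(Z > (32.38 − 45)/15.73) = P(Z > −0.80) = 78.9%. The contrast with within-arm variance rejects beyond about 1.983 × 15.73 = 31.2, which gives about 81%.

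**Step 4: simulation (400,000 trials per row, 35 per arm, mean booster effect 45).**

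| Gap D | Merged t-test | Three-arm contrast |
|---|---|---|
| 0 | 80.8% | 80.8% |
| 25 | 80.3% | 80.8% |
| 51 | 78.9% | 81.0% |
| 76 | 76.2% | 80.9% |
| 90 | 74.1% | 80.8% |

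A Welch version of the merged test gives 79.6% at D = 51. With a mean booster effect of zero and D = 51, the merged test rejects in 4.2% of trials and the contrast in 5.0%. With no effect in any arm, both reject in about 5%.

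**Step 5: unequal booster arms (illustrative).** At D = 51 with 40 participants in the better booster and 30 in the other, the merged mean targets (40 × 70.5 + 30 × 19.5)/70 = 48.6. With the sizes reversed it targets 41.4. Power of the merged test is about 85% and 72% respectively. The equally weighted contrast stays at about 81% either way.

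**Step 6: what the change does not cure.** If one booster gives 45 and the other nothing, the mean effect is 22.5. Power is about 27% merged and 29% with the contrast.

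**The case against.** The strongest reply is that nothing in the plan is wrong. The test is prespecified and valid, its power reproduces, and with equal arms the merged mean and the contrast give the same point estimate. The article does not say whether the t-test pools variances; with Welch the loss at a gap of 51 is about 1.4 points. All of this stands, and it keeps the point minor.

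A reader might infer more, and the documents do not support it:

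- **That the plan expects a gap of 51.** Section 2.8 gives 51 as a difference detectable with 105 participants. The primary objective is repeated versus single injection, and the difference between boosters is a further objective without direction or size.
- **That the loss is large.** Power near 74% needs effects of 90 and 0. The plan contains no such scenario, and 90 is twice the 45 for which it is powered.
- **That the arms are weighted by chance.** 105 is 3 × 35 and the power figures fit equal arms. The absence of a blocking statement from a condensed article is no evidence that arm sizes were left open. Unequal weighting follows only if the final counts are unequal.
- **That the second test is also at fault.** Borrowing the control arm's variance would raise its power from 79.0% to 79.4%. Leaving the control arm out also protects that test if the control SD differs.

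What survives the reply is that the merged test gives up some power whenever the boosters differ, and that the alternative gives up none when they do not.

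**Conclusion.** The point holds as a minor, free improvement. It is not an error in the plan: the planned test controls type I error (with equal arms it is at or below 5%), and the 80% is right for equal boosters. If the boosters differ by 51, the first test and gate has about 79% power instead of 81%. The loss is half a point at a gap of 25 and 5 to 7 points at gaps of 76 to 90. Unequal arm sizes would add a dependence of the target on those sizes. These figures rest on 35 per arm (except the 40:30 illustration), normal AUPC, a common SD of 76 and a mean booster effect of 45.

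**What to change.** In Section 2.9.1, replace the first Part 2 test with a linear model that has the three arms as a factor. Test the contrast (fixed-time + on-demand)/2 − control, using the within-arm residual variance (102 df with 105 participants). Use the same contrast for the hyperalgesia and allodynia AUCs in Section 2.9.2. The gatekeeping order and the fixed-time versus on-demand test may stay as planned.

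The cost is a sentence or two in the protocol or analysis plan before Part 2 is analysed, and one residual degree of freedom (102 instead of 103). No extra participants are needed. The change relies on equal SDs across arms, which Section 2.8 already assumes for the sample size. It should not be presented as a remedy for dilution when only one booster works.
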